## Abstract

**Background:**

Subclinical hypothyroidism is a common condition in patients with heart failure and is defined as elevated serum thyroid hormone (TSH) with normal circulating free thyroxine (FT4). Evidence on the effect of thyroid hormone treatment is lacking. We designed a randomized controlled trial to compare the efficacy and safety of thyroid hormone supplementation in patients with chronic heart failure complicated with subclinical hypothyroidism.

**Methods/design:**

Eligible participants were identified from the cardiology units of five study centers based on the following criteria: 18 years or older, systolic heart failure with NewYork Heart Association (NYHA) class II–III, left ventricular ejection fraction ≤ 40%, and subclinical hypothyroidism (TSH > 4.78μIU/ml, < 10 μIU/ml + FT4 level within reference range). Eligible patients will be randomly assigned in a 1:1 manner to receive thyroxine replacement therapy plus standard chronic heart failure (CHF) treatment or only standard CHF therapy. Levothyroxine will be administered at an initial dose of 12.5 μg once daily and will be titrated until TSH is within the normal range. The primary endpoints include the difference in distance of the six-minute walk test between 24 weeks and baseline. The secondary endpoints include differences in plasma NT-proBNP levels and serum lipid profiles, changes in the NYHA classification, cardiovascular death, re-hospitalization, differences in echocardiographic and cardiac magnetic resonance imaging measures, and Minnesota Living With Heart Failure Questionnaire (MLHFQ) results between 24 weeks and baseline.

**Discussion:**

ThyroHeart-CHF is designed as a prospective, multi-center, randomized, controlled clinical trial to study the efficacy and safety of thyroid hormone supplementation in patients with chronic heart failure complicated with subclinical hypothyroidism. The study findings will have significant implications for discovering the new therapeutic targets and methods of heart failure.

**Trail Registration:**

ClinicalTrials.gov, NCT03096613. Registered on 30 March 2017.

## Background

Heart failure (HF) is the leading cause of death among cardiovascular diseases, seriously endangering human health and life. The epidemiological characteristics of HF in China are similar to those in developed countries. In 2003, approximately 0.9% of Chinese adults suffered from various degrees of HF. Among subjects of the Framingham Heart Study, the 30-day mortality of HF was 10%, whereas 1-year mortality rates reached 20–30% [1]. In the past two decades, medication for HF has undergone tremendous changes from improving haemodynamics to biomimicry. Despite guidelines and recommended treatments, however, HF mortality has declined but remains at a high level. Therefore, further exploration and discovery of new therapeutic targets and methods for HF are the major issues and challenges we face.

Subclinical hypothyroidism (SCH; elevated TSH with normal circulating free thyroxine (FT3/FT4)), an early stage of clinical hypothyroidism lacking clinical manifestations, has become the new target of treatment for cardiovascular abnormalities. In 2005, we found that hypothyroidism can lead to the occurrence and development of HF even in the absence of heart diseases in animal experiments. The mechanisms of HF caused by hypothyroidism include coronary artery loss, impaired coronary artery flow, and non-adaptive myocardial changes [2]. Growing evidence suggests that hypothyroidism plays a crucial role in the development and progression of chronic HF and is associated with poor prognosis and even death [3, 4].

Epidemiological data have revealed that approximately 13–15% of patients with HF have subclinical hypothyroidism, especially elderly patients [5–8]. Subclinical hypothyroidism (TSH 8.59 ± 4.91 mIU/L) is an independent risk factor for death (hazards ratio = 2.869, 95% confidence interval 1.817–4.532) [9]. A similar conclusion was reported by Iervasi et al. [10] in a study following 3121 patients with heart disease for 32 months. The study also found that subclinical hypothyroidism (TSH 4.5–10 mIU/L) was a predictor of cardiovascular and all-cause mortality [10]. Rodondi et al. [11] reported that subclinical hypothyroidism was an independent risk factor for HF (hazards ratio = 2.33, *P* = 0.03) after 4 years of follow-up of 2555 non-HF patients.

The treatment strategy for HF patients with SCH is intractable given the misconception that SCH is only a simple negative feedback regulation in heart disease and the lack of clinical research on thyroid hormone replacement therapy for HF patients with SCH. American College of Cardiology Foundation (ACCF)/American Heart Association (AHA) guidelines for the management of HF recommended that thyroid function should be routinely assessed in patients with HF [12]. Animal studies and some non-randomized controlled clinical studies have confirmed the beneficial effects of thyroid hormone therapy on cardiac function [13–15]. Therefore, we hypothesized that thyroid hormone supplementation in patients with chronic HF complicated with subclinical hypothyroidism could improve exercise tolerance and quality of life. We use the six-minute walk test (6MWT) to evaluate exercise tolerance, which is particularly useful for measuring the response to medical interventions in patients with moderate to severe heart or lung disease. The 6MWT has also been used to determine the functional status of patients, as well as a predictor of morbidity and mortality [16]. We thus designed this prospective, multi-center, randomized, open labeled, controlled clinical trial to study the efficacy and safety of thyroid hormone supplementation in patients with chronic heart failure complicated with subclinical hypothyroidism.

## Methods/design

### Patient selection

Eligible participants will be identified from the cardiology units of five study centers (Fuwai Hospital, Beijing LuHe Hospital, The Second Hospital of Tianjin Medical University, The First Hospital of Hebe Medical University, Henan Provincial People’s Hospital). All individuals will have their thyroid function checked within 24 h of admission to the hospital or clinical visit. Eligible patients will meet the following inclusion criteria: (1) 18 years or older, (2) systolic HF with NewYork Heart Association (NYHA) class II–III, (3) left ventricular ejection fraction ≤ 40% by echocardiography during screening and randomization, (4) subclinical hypothyroidism (TSH > ULN, < 10 mIU/mL + FT4 level within reference range, (5) receiving standard therapy for chronic heart failure (CHF), reaching target dose or maximum tolerable dose, and (6) provide informed consent. The major exclusion criteria include acute HF or acute exacerbation of chronic HF within the past 2 weeks; scheduled cardiac resynchronization therapy or heart transplantation; history of malignant tumor or life expectancy under 12 months; currently taking medications that may affect thyroid function (LT4, carbimazole, propylthiouracil, amiodarone, lithium); pregnancy and lactation period; participation in another clinical trial within the past 30 days; contraindication or intolerance to evidence-based therapy for CHF, such as beta-blocker, angiotensin-converting enzyme inhibitor, or angiotensin receptor blocker; known hypersensitivity to the trial treatment(s) or diluents (when applicable), including placebo or other comparator drug(s); severe renal dysfunction (estimated glomerular filtration rate ≤ 30 ml/min/1.73 m^2^) or significant hepatic impairment (serum GPT > 120 U/L); and any disorder which, in the opinion of the investigator, might jeopardize a subject’s safety or compliance with the protocol.

Subjects’ participation in this study will be voluntarily and they will sign informed consent forms. No study-associated operation is allowed before written informed consent forms are obtained by the investigators. After informed consent forms are obtained, subject information, including medical history, physical examinations, and adjuvant examinations, will be collected by the investigators to confirm whether the subjects satisfy the inclusion/exclusion criteria. Subjects who conform to all inclusion criteria and do not meet any of the exclusion criteria will be enrolled in this study.

### Randomization

Patients enrolled in this study will receive 2-week standard HF treatment and be invited to have one more thyroid function test 10–14 days after the diagnosis of CHF. Eligible patients who sign written informed consent will be randomly assigned in a 1:1 manner across study centers to receive thyroxine replacement therapy plus standard CHF treatment or only standard CHF therapy. Randomization will be performed using an interactive web response system. Standard treatment for CHF will be administered in accordance with the “2016 ACC/AHA/HFSA focused update on new pharmacological therapy for heart failure” [17]. Levothyroxine will be administered at an initial dose of 12.5 μg once daily and will be titrated until TSH is within the normal range. The 6MWT will be performed at baseline and the 24-week clinical visit.

### Dosage and administration of levothyroxine

Levothyroxine will be administered at an initial dose of 12.5 μg once daily and will be titrated until TSH is within the reference range. All the participants will be required to have their thyroid function re-assessed at 4, 8, and 12 weeks to regulate the dosage of levothyroxine, whereas the thyroid status of those in the control arm will be only reviewed and recorded. Investigators will adjust the dosage of levothyroxine primarily based on TSH levels. Specifically, if TSH levels remain above the upper limit of the normal value, 12.5 μg/d of levothyroxine will be added. If TSH levels return to the normal range, the dosage of levothyroxine will be maintained. If TSH levels are below the lower limit of the normal value, the investigator will stop the levothyroxine prescription and thyroid function will be re-assessed 2 weeks later for further intervention (subjects remain in the thyriod hormone replacement therapy (TRT) group with regular thyroid function re-test and corresponding levothyroxine treatment until their TSH levels increase again). Patients who receive levothyroxine but have consistently elevated TSH levels during the 24 weeks will still be considered as “treated” and analyzed in the TRT group. In addition, the percentage of these patients in the TRT group will be calculated and reported, indicating the effectiveness of our conservative titrating strategy for subclinical hypothyroidism. However, these metrics are not the primary or secondary study endpoints. A flow chart of the study is provided in Fig. 1.

**Fig. 1 Fig1:**
[figure not shown]
Study Flowchart. *TSH* serum thyroid hormone, *L-T4* levothyroxine, *CHF* chronic heart failure

### Trial endpoints

#### Primary endpoints

The primary endpoint is the difference in the 6MWT distance between 24 weeks and baseline.

#### Secondary endpoints

Difference in plasma NT-proBNP levels between 24 weeks and baselineChange in NYHA classification at the 24th weekPercentage of patients experiencing cardiovascular death or HF re-hospitalizationPercentage of patients experiencing cardiovascular death, re-hospitalization for cardiovascular disease, severe arrhythmia, and strokeDifference in echocardiographic and cardiac magnetic resonance imaging measures between 24 weeks and baselineDifference in Minnesota Living With Heart Failure Questionnaire (MLHFQ) scores between 24 weeks and baselineDifference in serum lipid profiles (total cholesterol, low-density lipoprotein cholesterol) between 24 weeks and baseline

### Follow-up measurements

Clinical follow-up will be performed at weeks 4, 8, 12, and 24 after enrolment. The schedule for visits and evaluation of the subjects is presented in Table 1.

**Table 1 Tab1:**
[figure not shown]
Schedule of assessments

*HF* heart failure, *NT-proBNP* N-terminal pro-brain natriuretic peptide, *NYHA* New York Heart Association, *BMI* body mass index, *GPT* glutamic-pyruvic transaminase, *GOT* glutamic oxaloacetic transaminase, *TP* total protein, *ALB* albumin, *Tbil* total bilirubin, *Dbil* direct bilirubin, *CRP* C-reactive protein, *BUN* blood urea nitrogen, *Cr* creatine, *UA* uric acid, *GLU* glucose, *ALP* alkaline phosphatase

### Data management

An electronic data input system will be used in this study to collect data, and a remote input system will be established according to the electronic case report audited and approved by the sponsors. Subjects’ information required by the protocol should be input by investigators according to the guidelines for completing the electronic case report. The collected data in electronic Case Report Form (eCRF) will be audited and verified by referring to the source document by the clinical research associate of the project during a scheduled visit to ensure data integrity. After data are input into electronic care report tables, quality control and data audit procedures will be performed to ensure the accuracy and reliability of these data. Data managers will audit data deletion, logical error, and other data issues that need to be further explained using computers or artificially. Discovered data issues will be queried or sent to investigators or the Clinical Research Coodinator (CRC) via the electronic data capture system to resolve and update the data in Data Clarification Form (DCF). Investigators or the CRC will manage relevant issues and conduct questions and answers (Q&A) in the electronic data capture system. The updated operation of all data will be audited and preserved in this system. Data issues in the system will be resolved as soon as possible after all subjects complete the study, and the “clean” data will be exported. All data will be audited by the principal investigator, sponsor, data manager, and statisticians, after which the database will be locked.

### Statistics

The Biological Statistics Center of Fuwai Hospital will be responsible for the statistical analysis of the present study. All analyses will be performed based on an intention to treat. Thus, patients will be analyzed in the group to which they were randomized regardless of the treatment they received and whether they deviated from the protocol in any way. All efficacy analyses will be performed on the full analysis set, and safety analysis will be performed on the safety analysis set. The full analysis set includes the set of subjects who are in accordance with the principle of intentionality treatment (ITT principle). Covariance analysis adjusted for traditional risk factors will be used to compare the primary endpoint between two groups, and the absolute difference and 95% confidence interval will be given. In survival analysis, the Kaplan–Meier curve method will be used to calculate the time to clinical endpoints, and the multivariate Cox proportional hazards model will be further applied to estimate the hazard ratios. Continuous variables will be expressed as the mean ± standard deviation. Categorical variables will be described as the frequency or ratio. The normally distributed continuous variables will be compared by using two-sided Student’s *t*-test, and continuous variables that are not normally distributed will be compared using Wilcoxon rank test. Categorical variables will be compared using the two-sided likelihood ratio chi-squared test or Fisher exact test. All statistical analyses will be performed with SAS software, version 9.2 (SAS Institute, Cary, NC, USA).

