### Sample size

Sample size and power calculations for the study are based on the following assumptions: two-sided log-rank test; α = 0.05; randomization ratio of 1:1. The sample size calculation is based on the expected change in 6MWT distance at week 24. In another study, the mean difference between groups for the change in 6MWT distance from baseline at week 24 was 40 m with a standard deviation (SD) of 70 m [18]. Based on these assumptions, a sample of 62 subjects per group (124 in total) are required to detect a mean treatment effect of at least 40 m at week 24 with 80% power at a two-sided significance level of 5%, allowing for 20% drop-out.

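### The primary ANCOVA names an unlisted set of risk factors but not baseline six-minute walk distance, so nearly free precision is forgone

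*Protocol article*

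**What the plan says.** The Primary endpoints section defines a change score: "The primary endpoint is the difference in the 6MWT distance between 24 weeks and baseline". The Randomization section confirms that both measurements exist: "The 6MWT will be performed at baseline and the 24-week clinical visit".

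For the analysis, the Statistics section states: "Covariance analysis adjusted for traditional risk factors will be used to compare the primary endpoint between two groups". It does not say which factors these are. Neither baseline walk distance nor centre is named as a covariate anywhere in the article.

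The Secondary endpoints section lists further continuous changes from baseline: NT-proBNP, imaging measures, MLHFQ score and lipids. None is given its own method. The only stated rule that reaches them is the general one in Statistics. Where normality holds, it calls for a t-test; for the rest, the rule reads: "continuous variables that are not normally distributed will be compared using Wilcoxon rank test".

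On allocation, patients are "randomly assigned in a 1:1 manner across study centers". Stratification by centre is not stated.

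**The concern.** A change from baseline is usually negatively correlated with the baseline value: patients who walk unusually short distances at entry tend to gain, and those who walk unusually far tend to lose. Unless baseline is in the model, this relation stays in the residual variance, and any chance difference between the arms at entry carries into the estimated effect. The outcome's own baseline is normally the most useful covariate available. The article commits to an adjusted model, yet describes the adjustment by a phrase that is not defined and that, on its ordinary meaning, does not cover baseline walk distance.

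At stake are the width of the primary confidence interval, the sensitivity of the estimate to baseline imbalance in a trial of 124 patients, and whether a reader can tell which model is primary. The same loss arises for the continuous secondary endpoints if the general two-sample rule is applied to them. It matters most for NT-proBNP, which is taken here to be right-skewed.

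**Working it through.** **Inputs from the article (Sample size section).** The difference and spread of the change in walk distance: "was 40 m with a standard deviation (SD) of 70 m"; two-sided α 0.05; power 80%; drop-out 20%; 62 per group. The section names a log-rank test, but the figure is that for a difference in means.

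**Assumed, not in the article.** The correlation ρ between baseline and week-24 distance, taken from 0.5 to 0.9, and equal SDs at the two visits.

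**Step 1: reproduce the plan's figure.** n per group = 2 × (1.960 + 0.842)² × 70² / 40² = 48.07, rounded up to 49 evaluable. Allowing for drop-out, 49 / 0.8 = 61.25, rounded up to 62, or 124 in total. This matches. The SD used is that of the unadjusted change, so no credit was taken for covariates.

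**Step 2: gain from adding baseline.** With SD s at each visit, the change has variance 2s²(1 − ρ), and the residual after regression on baseline has variance s²(1 − ρ²). The ratio is (1 + ρ)/2, so the effective SD is 70 × √((1 + ρ)/2). Power is from the noncentral t at 0.8 × 62 = 49.6 evaluable per arm. The 95% half-width is 1.96 × SD × √(2/49.6).

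| Analysis | Variance ratio | Effective SD (m) | Power | Half-width (m) |
|---|---|---|---|---|
| Unadjusted change | 1 | 70.0 | 80.4% | 27.6 |
| Baseline, ρ = 0.5 | 0.75 | 60.6 | 90.2% | 23.9 |
| Baseline, ρ = 0.6 | 0.80 | 62.6 | 88.3% | 24.6 |
| Baseline, ρ = 0.7 | 0.85 | 64.5 | 86.3% | 25.4 |
| Baseline, ρ = 0.8 | 0.90 | 66.4 | 84.4% | 26.1 |
| Baseline, ρ = 0.9 | 0.95 | 68.2 | 82.4% | 26.9 |

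The comparator is a wholly unadjusted analysis. The stated model already adjusts for something, so these gains are upper bounds.

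**Step 3: chance imbalance.** Under the same assumptions, the slope of change on baseline is −(1 − ρ). A baseline difference of D metres therefore shifts the change-score contrast by (1 − ρ)D. For an illustrative D of 15 m, the shift is 7.5 m at ρ = 0.5, 4.5 m at 0.7 and 1.5 m at 0.9, against a target effect of 40 m. An imbalance of this size is unremarkable: at ρ = 0.5 the implied single-visit SD is 70/√(2 × 0.5) = 70 m, and the standard error of the baseline difference is 70 × √(2/62) = 12.6 m.

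**Step 4: NT-proBNP, illustration only.** Assumptions: log-scale SD 1 at each visit, a 33% reduction (log 0.67 = −0.400), and 50 per arm. If the variable is skewed, the article's own rule leads to the Wilcoxon test, so that is the fair comparator (simulated, 10,000 trials per ρ, on raw change). For log-scale ANCOVA the standard error is √(1 − ρ²) × √(2/50). The standardised effects are 2.31, 2.80 and 3.34, against a critical t of 1.985 on 97 degrees of freedom.

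| ρ | Wilcoxon on raw change | Log-scale ANCOVA |
|---|---|---|
| 0.5 | 37% | 63% |
| 0.7 | 55% | 79% |
| 0.8 | 72% | 91% |

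**Centre.** No between-centre variance is given, so no gain from centre can be computed.

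**The case against.** The strongest reply is that a one-paragraph methods summary in a journal article leaves the covariate list to a fuller document, and that silence on baseline is not exclusion. That stands in part. A reader might infer that baseline distance and centre are ruled out, but the text only fails to name them. A reader might also infer that covariates will be chosen once results are known. The article does not show this, since a closed list may exist elsewhere. What remains is that the article does make a choice for its primary model, describes it by an undefined phrase, and leaves out the covariate with the clearest claim.

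Second, nothing planned is lost. This stands: a reader who infers that the trial is underpowered is mistaken, because the sample size rests on the unadjusted SD. Randomization also keeps the change-score contrast unbiased on average, and its standard error already allows for chance imbalance. Adjustment narrows that error and removes the realised imbalance from the estimate; it does not cure a bias.

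Third, the t-test/Wilcoxon rule is general, and might describe baseline comparisons rather than the secondary endpoints. It is not tied to any endpoint, so the article cannot be said to assign unadjusted tests to NT-proBNP or the others. It is, however, the only stated method that reaches them.

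Fourth, adjustment for centre is not required by the stated design, because stratification is not stated. This stands in full.

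**Conclusion.** The point holds as a forgone gain, not as an error in the sample size. The primary model should name baseline walk distance and does not. The benefit is at most about 10 percentage points of power at ρ = 0.5 and about 2 points at ρ = 0.9, with the 95% half-width falling from 27.6 m to between 23.9 m and 26.9 m. These figures rest on an assumed ρ, equal SDs at the two visits, and a comparator with no adjustment at all. Protection against realised baseline imbalance is a further benefit, and it shrinks in the same way as ρ rises.

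For the continuous secondary endpoints, adjustment for own baseline is a sound improvement on the only rule stated. The NT-proBNP figures show direction and rough size under invented inputs and are not a forecast. No claim is made about centre beyond making its inclusion depend on stratification. The change is worth making because it costs almost nothing.

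**What to change.** - **Primary model.** State it as ANCOVA of week-24 six-minute walk distance (or of the change, which gives the same treatment estimate once baseline is included) on treatment and baseline distance. Add centre only if randomization is stratified by centre. Report the adjusted difference with its 95% confidence interval.
- **Other risk factors.** Either fix a short, named list for the primary model before the data are analysed, or move them to a sensitivity analysis.
- **Continuous secondary change endpoints.** Use the same model with each endpoint's own baseline as covariate. Analyse NT-proBNP on the log scale and report a ratio of geometric means. Say that the t-test/Wilcoxon rule does not apply to these endpoints.

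**Cost.** Wording changes and a few degrees of freedom. These are change-from-baseline endpoints, so their baselines are needed already; no new visits, measurements or patients are required, and the sample size can stay as it is.
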